## Abstract

**Background:**

Several types of psychotherapy have been proven successful in the treatment of personality disorders in younger age groups, however studies among older patients are lacking. We developed a group schema-focused therapy (SFT) enriched with psychomotor therapy (PMT) for older adults with cluster B and/or C personality disorders. This paper describes the design of a randomized controlled trial (RCT). We will evaluate the (cost-)effectiveness of this therapy protocol in specialized mental health care. We hypothesize that our treatment program is cost-effective and superior to treatment as usual (TAU) in reducing psychological distress and improving quality of life in older adults treated to specialized mental healthcare.

**Methods:**

A multicenter RCT with a one-year follow-up comparing group schema-focused therapy enriched with psychomotor therapy (group SFT + PMT) and TAU for adults aged 60 years and older who suffer from either a cluster B and/or C personality disorder. The primary outcome is general psychological distress measured with the 53-item Brief Symptom Inventory. Secondary outcomes are the Schema Mode Inventory (118-item version) and the Young Schema Questionnaire. Cost-effectiveness analysis will be performed from a societal perspective with the EuroQol five dimensions questionnaire and structured cost-interviews.

**Discussion:**

This study will add to the knowledge of psychotherapy in later life. The study specifically contributes to the evidence on (cost-) effectiveness of group SFT enriched with PMT adapted to the needs of for older adults with cluster b and/or c personality.

**Trial registration:**

Netherlands Trial Register NTR 6621. Registered on 20 August 2017.

## Background

The prevalence rate of personality disorders among community-dwelling older people is estimated at 8% [1] and varies between 33 and 58% among older people referred to specialized mental health care [2–4]. The disease burden due to personality disorders is high for patients (lowered quality of life, high levels of psychological distress and a high suicide risk) as well as for society (increased medical consumption and informal care) [5, 6]. For example, maladaptive personality traits are associated with a 16–30% increase in somatic healthcare consumption among older adults [7, 8]. Adequate detection and treatment is therefore warranted from both a patient and societal perspective. Even in specialized mental health care for older adults, personality disorders often remain undiagnosed and undertreated [9, 10]. Among younger patients several psychological therapies, among which schema focused therapy (SFT) have been developed that effectively reduce the burden of personality disorders [11, 12]. SFT addresses how early maladaptive schemas influence daily life and interpersonal relationships. Schemas pertain to one’s core conceptions of self, others and the world. They are formed in childhood and adolescence. In case of adverse circumstances, maladaptive schemas and associated coping styles will develop to survive (emotionally) which later on, in a healthier environment will lead to interpersonal dysfunctional coping and emotional instability. SFT helps patients to identify their most important maladaptive schemas and to respond in a more adaptive manner when these maladaptive schemas are triggered in daily life.

Review studies in adults (< 60 years) on the treatment for personality disorders concluded that SFT improves quality of life for the borderline personality disorder. They found a recovery from psychological symptoms and that it was less expensive compared to usual care [12]. The aforementioned studies focused on the borderline personality disorder [11] for which SFT was originally developed [13]. However, effectiveness of SFT has also been proven for the avoidant personality disorder [14], mixed group personality disorders [15], and more recently for the chronic mood- and anxiety disorders [16, 17]. Although SFT is generally delivered in an individual format, group SFT is considered to speed up and amplify the effects of individual SFT [18]. Even so-called short-term group SFT [19] is associated with improvements in affective symptoms as well as personality pathology. Studies in younger and middle aged patients which tested the association between the effect of SFT and age did not find a significant impact of age [18, 20]. Extrapolation of these findings to older samples may suggest that SFT also remains effective in later life. Of all psychotherapies focused on personality disorders, SFT is considered most relevant for geriatric practice due to its favorable effects on comorbid, often longstanding affective disorders [21–23]. To date, only three uncontrolled studies of SFT among older adults have been published [9]. These studies point to favorable effects of SFT in later life. First, among 51 depressed inpatients, SFT led to improvement of depressive symptoms, anxiety and five out of the seven maladaptive schemas [24]. Second, among 31 Dutch older outpatients, group SFT improved psychological distress with effect-sizes similar to those reported for younger patients. Moreover, changes in early maladaptive schemas mediated change in psychological distress in this latter study [21]. Third, in a multiple-baseline case series study among 8 older persons suffering from a cluster C personality disorder, psychopathology remained stable during an extended baseline period, while psychopathology significantly diminished during treatment and follow-up [25].

Although these studies among older patients are promising, some caution is needed since no randomized controlled studies evaluating SFT in later life have been conducted yet [9]. Therefore, we decided to perform such a randomized controlled trial and to present its study design here. SFT protocols examined among older patients up to now highly relied on cognitive techniques. Since cognitive techniques may become less effective with increasing age [26], we added several experiential techniques. These techniques are considered powerful methods to change early maladaptive schemas in older adults [21]. Not only did we add experiential techniques to the traditional, verbal SFT approach, we also enriched our treatment protocol with PMT. By offering PMT, patients will experience how their schemas influence their behavior and feelings. The ‘learning by doing’ approach offers opportunities to try out new behaviors [27]. Moreover, discovering the origin of feelings and physical sensations is an important therapeutic mechanism of SFT. PMT contributes to this important ingredient of SFT, by using bodily awareness and physical activities to let patients experience the way they tend to behave [28]. During the preparation phase of this trial, we ran five treatment groups to refine our protocol and test its feasibility. Participants of these pilot groups highly appreciated the psychomotor therapy, the experiential techniques and the adaptation of SFT to a geriatric population, in general.

### Study objectives

The aim of this article is to describe the design of a RCT examining the (cost-)effectiveness of group SFT enriched with PMT compared to treatment as usual for older patients suffering from a cluster B and/or C personality disorder. We hypothesize that our treatment program is cost-effective and superior to treatment as usual (TAU) in reducing psychological distress and improving quality of life in older adults treated to specialized mental healthcare.

## Methods

### Design

We designed a multi-center randomized controlled trial with two parallel treatment groups: 20 sessions of group SFT enriched with PMT delivered over a 6-months period, versus treatment as usual (TAU) for older adults with cluster B and/or C personality disorders in specialized mental health care. Primary outcome is general psychological distress. In addition, cost-effectiveness of the intervention from a societal perspective is evaluated. Outcome measurements will be administered pre- and post-treatment as well as at 6 and 12 months post-treatment. Six mental health care organizations in the Northern Netherlands agreed to participate, one university department of geriatric psychiatry (University Medical Center Groningen) and five affiliated mental health organizations (GGZ Friesland van Andel department, GGZ Drenthe, Lentis, Dimence and Mediant). The study has been approved by the Medical Ethics Committee of the University Medical Center Groningen on May 12th, 2017 (M17.212189) and was registered in the Dutch Trial Register on August 20th, 2017 (NTR 6621).

### Study population

Eligible are patients, 60 years or older with a cluster B and/or C personality disorder according to the DSM-5 who are referred to or are currently treated at an outpatient clinic for geriatric psychiatry of the participating centres in the Netherlands. According to DSM-criteria, the criterion threshold for diagnosing a personality disorder in older patients is too strict [29, 30]. For that reason we will also include older patients falling short one content criterion for a specific cluster B and/or C personality disorder, provided that they meet the general diagnostic criteria for a personality disorder (hereafter ‘subthreshold cluster B/C personality disorder’). Older patients generally endorse fewer specific personality disorder criteria than younger age groups (29% of the criteria contain measurement bias in older age groups), while the latent variable structure for each personality disorder suggests a similar severity level of personality pathology [30]. Specific inclusion criteria are: 1) age of 60 years or above; 2) cluster B or C personality disorder (or falling one content criterion short) as confirmed by the Structured Clinical Interview for DSM-5 for personality disorders (SCID-5-PD) [31] 3) mentally able to adhere to the group SFT treatment schedule and to fill out the schema (mode) questionnaires and 4) giving informed consent after having received oral and written information. Exclusion criteria are: 1) severe current mental illness, including bipolar I disorder, psychosis, or substance abuse disorders needing clinical detoxification; 2) an established neurodegenerative disorder; 3) cognitive impairment defined as a sum score below 23 points on the Montreal Cognitive Assessment (MoCA) battery [32]; 4) having received schema-focused therapy in the previous year or during the current illness episode; and 5) suicide risk interfering with adequate treatment delivery. Physical restraints or physical frailty are no exclusion criterion. Despite the group format, the PMT will be individually adapted so that even the frailest patients can participate.

### Recruitment

Mental health professionals working at the different sites can inform patients about the study when a cluster B or C personality disorder is suspected. After having received oral and written study information from their mental health professional interested potential eligible patients will get an appointment with the clinical psychologist at their clinic. During this screening session, the in- and exclusion criteria for the study are formally checked by administering amongst others the SCID-5-PD and MoCA and any remaining questions the patient has about the study are answered. For patients not meeting the in- and exclusion criteria the study ends after this screening session. Patients eligible for the study, will be given another 2 weeks to consider participation. Patients willing to participate in the study, will be asked to sign informed consent and are put on a waiting-list. Only the patients who gave written informed consent are included in the study. The data from the screening appointment, will be passed on – anonymously – for inclusion in the study database. When a minimum of 8 and maximum of 16 patients have given informed consent at a specific site, baseline measurements will be conducted, after which participants will be randomized (see flowchart) Fig. 1.

**Fig. 1 Fig1:**
[figure not shown]
depicts the flowchart of the study

### Sample size calculation

The only RCT comparing group SFT with TAU was conducted among younger adults with borderline personality disorder and found a between group Cohen’s *d* effect size (ES) of 2.0 on the Brief Symptom Inventory (BSI-53) [33]. For our power analysis, we tuned down the expected ES to 0.5 (medium effect) for two reasons. First, the ES of 2.0 was partly due to absence of an effect of TAU [34] while meta-analysis of psychotherapy in geriatric psychiatry shows an average pre-post ES of 0.4 for TAU [17]. Second, an open study on group SFT reported a pre-post Cohen’s *d* ES of 0.8 among older adults with mixed cluster B and C personality disorders [21]. Applying a 2-sided alpha of 0.05 and a power of 80% to detect an ES of 0.5, requires 63 patients per arm. Although compensation for dropout is not necessary according to the CONSORT criteria when performing intention to treat analyses (http://www.consort-statement.org/), we aim to include 140 patients in order to compensate for 10% early dropouts during the waiting-list period. Differences in the scores between the intervention and control group on the various outcome measures (BSI-53, EQ-5D-5 L, YSQ and SMI) will be analyzed using linear mixed-models accounting for missing data and relevant confounders.

### Randomisation, blinding and treatment allocation

A stratified block randomisation will be performed aimed to assign participants evenly (1,1) over the two conditions [35]. Randomisation will be performed per study site and stratified by the presence of a full versus subthreshold cluster B/C personality disorder (PD – 1 criterion). Participants will be randomized in blocks when 8 to 16 consecutive patients have consented to participate at a specific study site. Randomisation will be performed centrally using online randomisation software QuickCalcs of GraphPad (http://www.graphapd.com/quickcalcs/randMenu).) by an independent investigator who will be blind to patient characteristics. Patients will be randomized in even patient numbers per stratum. In case of an uneven number of participants per stratum, the next even number of patients will be randomised and the last allocation will be forwarded to the next block randomisation with an uneven number of patients within that stratum. After randomisation, patients and their responsible geriatric psychiatrist or psychologist will be informed of their allocation. The therapists delivering the intervention will be informed which patients can be invited for group SFT + PMT.

### Group Schema-focused therapy enriched with PMT

Two individual pre-treatment sessions without PMT take place before the group sessions. These are meant to make a personal treatment plan based on administering the Young Schema Questionnaire (YSQ) and Schema Mode Inventory (SMI) (see Mediators section below) and to explain the concept of group SFT enriched with PMT in more detail. The subsequent group interventions comprise 20 sessions over a period of 26 weeks. The first 18 sessions will be provided weekly after which two follow-up sessions are given at week 22 and 26. Each treatment session consists of a 2 h group session SFT and 1 h group session PMT, with a 15-min break in between. Treatment is provided according to a detailed protocol. This protocol is highly structured and based on the Dutch protocols short cognitive schema-focused group therapy [36] and experiential techniques [37, 38]. During the initial group sessions, patients will be further educated about the schema model, specifically in relation to their own three predominant schemas and coping styles (called ‘modes’ in schema focused therapy). In the second treatment phase the patients maladaptive schemas will be triggered and patients will be taught to respond in a more adaptive manner. In this treatment phase the ‘experiential imagery rescripting’ and ‘chair interventions’ will be conducted [37, 38]. All patients receive a personal schema-focussed therapy workbook for older adults. This workbook will be extended every session with a summary of the session information and homework assignments. The patients will write a weekly summary of their therapy process and fill in a ‘severity score form’. On this form patients rate the severity of their 3 predominant schemas and maladaptive modes. Based on clinical experience with older persons, geriatric themes like loss of a role in society, loss of loved-ones, comorbid somatic diseases and sociocultural beliefs in the treatment of elderly, are integrated in the treatment protocol [39, 40]. Furthermore, the protocol has been enriched with PMT to overcome the limitations of verbal therapy. During PMT, the psychomotor therapist sets up individual and group-based physical interventions to facilitate that patients experience their schemas and modes. Continuity between the verbal and psychomotor sessions is guaranteed by participation of the psychologist in the PMT as co-therapist. This way the observations pending PMT can be further analyzed in the verbal sessions.

### Treatment as usual

Treatment as usual (TAU) will be unrestricted as long as no group SFT is provided. Usually this means that a multidisciplinary team will determine the best treatment for each patient. This can be either psychotherapeutic or drug treatment, individual or group treatment, outpatient-, day- or inpatient treatment or any combination deemed necessary. The treatment provided will be registered, to facilitate interpretation of results. From our clinical experience, we expect that TAU will mainly consist of structured and supportive case-management of personality problems or treatment restricted to (comorbid) axis I psychiatric disorders, ideally according to disorder specific guidelines.

### Therapists, training and supervision

All interventions in the experimental group are provided by psychologists with a minimum of 2 years post graduate clinical training in combination with fully licensed and registered psychomotor therapists. During the verbal SFT sessions, a co-therapist will participate. Co-therapists are generally also psychologists but psychotherapeutic oriented nurse practitioners experienced in group treatment are also allowed. One of the psychologists providing verbal SFT will also participate as co-therapist in the PMT sessions. All psychologists and psychomotor therapists receive a two-day training led by the first author, a clinical psychologist who is also a licensed schema-focused therapist. The psychomotor therapists are trained by the third author. This training covers how to deliver a structured SFT program, training of the SFT adaptations to older adults and PMT techniques. The training is supported by video material of verbal SFT and PMT techniques. All therapists receive a manual with the treatment protocol, including a detailed description of all sessions divided in a SFT and a PMT section. Moreover, to improve protocol compliance, the SFT-interventions provided must be ticked off on standardized forms (part of the manual) per session. Session attendance of the individual patients will also be recorded by the therapists. During the study, all therapists will participate in a monthly supervision program provided by the first and third author. Furthermore, all SFT and PMT group sessions in the intervention arm will be audiotaped and saved for evaluation. Of each therapy group two audiotapes will be randomly selected and rated by independent psychologists on protocol compliance. All interventions listed in the treatment manual for the selected session will be evaluated on whether or not the intervention was delivered and the quality of that deliverance, as rated on a scale ranging from 0 (not delivered) to 10 (delivered excellently). A total of at least 10 tapes will be rated by two raters to assess the interrater reliability, as expressed the intra class correlation coefficient (ICC) [41].

### Assessments

Data are collected at the following moments: at the screening, baseline (T1), at the end-of-treatment (T2, i.e. 6 months after baseline for the TAU group), and finally at 6- and 12-month follow-up (T3 and T4). Many outcomes consist of self-report measures. Some are assessed by structured telephone interviews conducted by research assistants who will be blind about the treatment allocation of the interviewed patient. These interviews include assessment of socio-demographic characteristics and psychiatric history (at baseline only) as well as medical consumption and costs in the past 3 months. Personal information about potential and enrolled participants will be stored confidentially. Table 1 shows the questionnaires used at each assessment.

**Table 1 Tab1:** .shows the questionnaires used at each assessment

	Time of assessment				
	Screening	Baseline	Post treatment assessment	6-month Follow-up	12-month Follow- up
Primary outcomes					
Psychological distress: BSI-53		X	X	X	X
Health-related quality of life: EQ-5D-5 L		X	X	X	X
Medical consumption & costs		X	X	X	X
Secondary outcomes					
Life satisfaction: Cantril’s Ladder		X	X	X	X
Mental wellbeing: WEMWBS		X	X	X	X
Personality functioning: SIPP-SF		X	X	X	X
Interoceptive body awareness: MAIA		X	X	X	X
Psychotropic drug use & treatment received					
Mood variability: Mood-Zoom		X	X	X	X
Characteristics					
Personality disorders: SCID-5-PD Cluster B & C	X				
Mental disorders: MINI-Plus	X				
Cognitive screening: MoCA	X				
Psychiatric treatment history: telephone interview		X			
Socio-demographics: telephone interview		X			
Chronic illnesses: LASA questionnaire		X			
Early life-events: NEMESIS questionnaire		X			
Alcohol use: AUDIT		X			
Current smoking: NEMESIS questions		X			
Physical activity: NEMESIS question		X			
Personality traits: PID-5-SF		X			

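### T2 to T4 run from end of treatment in the SFT+PMT arm but from baseline in the TAU arm, so SFT+PMT patients are assessed somewhat later after baseline

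*Protocol article*

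**What the plan says.** - **Assessment times.** The Assessments section sets T2 "at the end-of-treatment (T2, i.e. 6 months after baseline for the TAU group", with T3 and T4 as the 6- and 12-month follow-up visits. The Design section gives the anchor for the later visits: "Outcome measurements will be administered pre- and post-treatment as well as at 6 and 12 months post-treatment".
- **Baseline.** Under Recruitment, once 8 to 16 patients at a site have consented, "baseline measurements will be conducted, after which participants will be randomized". The randomisation section then has patients and their clinicians informed, and the therapists told whom they can invite.
- **Treatment in the SFT+PMT arm.** The intervention section says: "Two individual pre-treatment sessions without PMT take place before the group sessions". It continues: "The subsequent group interventions comprise 20 sessions over a period of 26 weeks". The last two sessions are tied to the end of that period: "The first 18 sessions will be provided weekly after which two follow-up sessions are given at week 22 and 26". The Design section summarises this as "20 sessions of group SFT enriched with PMT delivered over a 6-months period".
- **Economic horizon.** The economic evaluation section sets a single horizon of 18 months for the comparison.
- **Mediators.** The Mediators section schedules the schema and mode questionnaires, in the experimental arm only, before treatment and at 3, 6 and 12 months counted from baseline.

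**The concern.** T2 is tied to a treatment event in one arm and to the calendar in the other. Those two points coincide only if nothing takes time between baseline and the first group session, and the protocol places several steps there. T3 and T4 count from the end of treatment, so the same gap carries forward to every follow-up visit.

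The main thing at stake is the clinical contrast. The analysis tests the interaction of time and study arm. If visits are coded by their nominal times, SFT+PMT patients have had longer to change by each visit, and any change that would have happened anyway in that extra time is counted as treatment effect.

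The economic evaluation is a second, conditional matter. TAU T4 falls at the 18-month horizon and SFT+PMT T4 falls after it, so the rule for where accrual stops begins to matter.

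The mediators add a further inconsistency. Within the SFT+PMT arm they run on a baseline clock while the outcomes run on an end-of-treatment clock.

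**Working it through.** **Inputs from the protocol article**
- TAU T2: 6 months after baseline (Assessments).
- SFT+PMT T2: end of treatment (Assessments). The group programme lasts 26 weeks and follows two individual sessions (intervention section).
- T3 and T4: 6 and 12 months after treatment (Design).
- Economic horizon: 18 months (economic evaluation section).
- Average pre-post effect of usual care: 0.4; planned between-group effect: 0.5 (Sample size calculation).

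**Input not in the document:** the lead-in *g*, the time from baseline to the first group session. I use 2 and 4 weeks as assumptions.

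**1. The plan's own figures.** TAU T4 = 6 + 12 = 18 months, which reproduces the horizon. One month is 365.25 / 12 / 7 = 4.348 weeks, so 6 months = 26.09 weeks, and the 26-week programme is 26 / 4.348 = 5.98 months. With *g* = 0 the arms coincide. The whole discrepancy is therefore the lead-in.

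**2. Visit times in the SFT+PMT arm.** T2 = 26 + *g* weeks; T4 = T2 + 12 months.

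| *g* (weeks, assumed) | SFT+PMT T2 | Gap to TAU T2 | SFT+PMT T4 |
|---|---|---|---|
| 0 | 26 weeks (5.98 months) | -0.09 weeks | 17.98 months |
| 2 | 28 weeks (6.44 months) | 1.91 weeks | 18.44 months |
| 4 | 30 weeks (6.90 months) | 3.91 weeks | 18.90 months |

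**3. Size on the clinical outcome.** Assume that the usual-care effect of 0.4 builds up evenly over 26 weeks, and that it is on the same SD scale as the planned effect. The extra change in SFT+PMT from time alone is 0.4 × *g* / 26.
- *g* = 2: 0.4 × 2 / 26 = 0.031 SD, and 0.031 / 0.5 = 6% of the planned effect.
- *g* = 4: 0.4 × 4 / 26 = 0.062 SD, and 0.062 / 0.5 = 12% of the planned effect.

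The direction favours SFT+PMT as long as patients are still improving at that point.

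**4. Size on QALYs, only if each arm is summed to its own T4.** Extra QALY = utility × gap / 52.18 weeks. At an assumed utility of 0.7 (range 0.5 to 0.9):
- *g* = 2: 0.7 × 1.91 / 52.18 = 0.026 (0.018 to 0.033).
- *g* = 4: 0.7 × 3.91 / 52.18 = 0.052 (0.037 to 0.067).

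If both arms are cut or interpolated at 18 months, this term is zero.

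**5. Sample size.** It is untouched: 63 per arm is 126, and 126 / 0.9 = 140, as planned.

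**The case against.** The case against is substantial, and much of it stands.

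- **The lead-in is not stated and may be short.** This stands. The protocol does not say how far apart the two individual sessions are. The long wait for enough patients falls before baseline, because baseline is taken only once a site has 8 to 16 consenting patients. A reader might infer a wait of many weeks after baseline, but the text does not support it.
- **A reader might infer that the arms have different QALY and cost horizons.** The document does not say so. It sets one 18-month horizon and uses the same 3-month cost recall in both arms. Horizons would differ only if accrual ran to each arm's own T4, and no section states that.
- **A reader might infer that T2 moves to the day a patient stops treatment, so that visit time depends on adherence.** No section says this. The programme has a scheduled end at week 26 and the analysis is by intention to treat, so the scheduled end is the natural reading.
- **Random coefficient models can use actual observation times, and natural change may be small.** This stands in part. In the eight-patient case series cited in the Background, psychopathology was stable over an extended baseline. Against that, the sample size section itself expects improvement under usual care. Modelling actual dates reduces the problem, but it relies on the assumed shape of change and cannot make visits held at different times directly comparable.

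What survives is the arm-dependent anchor. It is a visit rule that the protocol has already fixed, not an analysis detail left for later.

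**Conclusion.** The point holds in a limited form. Outcome visits are anchored to end of treatment in the SFT+PMT arm and to baseline in the TAU arm. By the protocol's own sequence of steps, SFT+PMT visits fall later after baseline at T2, T3 and T4, and T4 in that arm falls past 18 months.

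The size cannot be derived from the document, because the lead-in is not given. For an assumed lag of 2 to 4 weeks and even accrual of the usual-care effect, the bias at T2 is about 0.03 to 0.06 SD in favour of SFT+PMT, or 6% to 12% of the planned effect. That is modest and would not by itself create an effect of 0.5. The QALY figures are conditional on uncut accrual and should not be read as a bias in the stated plan. The change is worth making because it is cheap and because later analysis can only partly repair visits held on different clocks.

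**What to change.** 1. Schedule T2, T3 and T4 on one clock for both arms, whether or not treatment is completed. Either option works:
   - fixed times from baseline or randomisation (6, 12 and 18 months), which also fits the baseline clock already used for the mediators; or
   - one T2 date per site batch, for both arms, set by the scheduled end of that batch's SFT+PMT group, with T3 and T4 6 and 12 months later. Patients are randomised in site batches, so such a date is available.
2. Use actual assessment dates as the time variable in the mixed model.
3. State that QALYs and costs are computed to exactly 18 months from baseline in both arms.

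**Cost.** This changes a scheduling rule and some analysis wording, with no extra visits and no change to 63 per arm or 140 in total. Some visits move by a few weeks. With fixed times from baseline, T2 may fall slightly before the last SFT+PMT session. With batch dates, T4 falls slightly after 18 months in both arms, so the cut at 18 months is then essential.
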